### Participants and Procedures

In phase 1, a panel of 8-12 experts, comprising nurses, physicians, and pharmacists, evaluated the relevance and clarity of the proposed items derived from the literature review (content validity). The experts provided written consent to use their sociodemographic and professional characteristics for scientific reporting, as content validity is closely linked to the characteristics of the involved experts. This phase cannot be anonymous to ensure transparency, and variables such as sex, age, academic title, experience in studies testing content validity, and experience in oral anticoagulation were collected.

Once adequate content validity was established (December 2023), data collection commenced at the IRCCS (Istituto di Ricovero e Cura a Carattere Scientifico [Institute for Research and Healthcare]) Policlinico San Donato, using 2 cross-sectional data collection rounds using web surveys. A convenience sampling procedure was used, disseminating the web surveys through social media campaigns, newsletters, and flyers of associations involving anticoagulated patients, such as “Associazione Italiana Cardiopatici Congeniti” (AICCA). Participants for the second round were selected based on the same approach, with communication to prevent overlapping responses from participants who completed the survey.

Quality control measures have been implemented to ensure the integrity and quality of the data collection process: automatic data validation checks are included in the survey software to ensure that all responses are complete and adhere to the required format; unique identifiers were used for each participant to prevent duplicate responses in the dataset; and after data collection, statistical analyses were performed to identify any outliers or inconsistencies in the responses, which were then reviewed for accuracy.

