### Sample Size

The sample size for phase 1 will be 8-12 experts. The sample size required for phase 2 to perform the Mokken scaling analysis was determined considering the 20 items derived from phase 1 (content validity phase). A simulation-based power analysis was performed in R (R Foundation for Statistical Computing; library “Mokken”), as shown in Multimedia Appendix 1. The aim of the simulation was to estimate a sample size that would provide sufficient statistical power, set at 0.8, to detect a minimum H coefficient of 0.3, indicative of a moderate scale according to Mokken’s hierarchy. The H coefficient in Mokken scaling analysis measures the strength of the hierarchical relationship among items in a scale as it quantifies the extent to which items form a cumulative scale. A custom simulation function was created using R statistical software, with the following parameters defined: 20 items, initial sample (n= 200), number of simulations=100, desired power=80%, minimum H coefficient=0.3, and maximum number of iterations=30. For each simulation iteration, the function generated a matrix of binary data representing responses to the 20 items, with responses simulated under a simple random model (ie, the probability of success was 0.5 for each item). The results from the simulation suggested that a sample size of 500 patients would be needed to achieve the desired power of 0.8 for our MSA. The MSA procedure will help reduce the number of items to the first 10-15 items that define the preparedness for self-monitoring and self-management of oral anticoagulation in adult patients. The required sample size for the second round of data collection will be determined through Monte Carlo simulations, aiming to achieve a power of 0.8 for the confirmatory factor analysis (CFA) model.

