### Data Analysis

The data analysis will involve the use of various statistical methods to develop and validate the PERSONAE scale.

For the first data collection round, MSA will be conducted using the “mokken” package in R [23]. MSA allows for the hierarchical evaluation of items, and the most relevant items that measure preparedness for self-monitoring and self-management of oral anticoagulation will be selected for the PERSONAE scale [24]. Loevinger’s coefficient of homogeneity function will be used to assess the scalability of the items. Monotonicity violations will be checked, and violations below 80 will be consistent with the requirements of a Mokken scale [23,25]. Loevinger’s coefficients of homogeneity (H) at the scale, item, and pairs of items level will be computed, where H values equal to or greater than 0.3, 0.4, or 0.5 indicate weak, moderate, or strong scales, respectively [23,25]. Item pairs violating monotonicity will be excluded, and floor and ceiling effects in data distribution will be assessed. Invariant item ordering (IIO) will be performed to further narrow down the pool of questions based on monotone homogeneity [25]. The IIO procedure will remove items one at a time until no significant violations are found. The Htrans (H^T^) coefficient will express the accuracy of the IIO selection, and H^T^>0.3 will denote proper IIO process and consistent Mokken scales. The final set of questions will be used to calculate ρ coefficients for reliability using the Molenaar-Sijtsma technique [26]. This approach is particularly adequate for assessing reliability in MSA because it provides a robust estimate of the internal consistency for nonparametric scales. The Molenaar-Sijtsma technique is well-suited for evaluating the scalability and reliability of the items within the scale, ensuring that the PERSONAE scale reliably measures the construct of preparedness for self-monitoring and self-management of oral anticoagulation.

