CFA will be used to cross-validate the plausible unidimensional structure of the PERSONAE scale derived from the MSA, theoretically containing 10-15 items, using Mplus 8.1 (Muthén and Muthén, 2017). An unrestricted and unspecified model will be used with a maximum likelihood robust estimation of parameters. A confirmatory factor analysis with covariates will be used to estimate measurement invariance between subgroups if linear relationships between participant characteristics and the scale’s total score are detected [27]. Modification indices will be explored to identify items causing a violation of invariance. Items causing invariance will be evaluated for possible deletion from the final scale. The adequacy of confirmatory factor analyses in explaining sample statistics will be assessed using various fit indices, such as chi-square, chi-square/degree of freedom, comparative fit index, Tucker-Lewis index, and root mean square error of approximation [28]. Invariance testing based on different levels of CCI and other potential confounders will be considered if needed and is feasible to ensure that the scale functions equivalently across groups with varying levels of comorbidity and demographics.

Missing data will be managed using an available-case approach for missingness lower than 5% or regression imputations for missingness equal to or higher than 5%, assuming missing at random. The significance level for all analyses will be set at 5%. The software used for the analysis will include Mplus (version 8.1, Muthén and Muthén), IBM SPSS Statistics for Microsoft Windows version 27, and R (version 4.2.1, R Foundation for Statistical Computing).

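### Regression imputation at 5% or more missingness, read in the usual way, inflates H, the statistic that selects the items and grades the scale

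*Protocol article*

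**What the plan says.** The Data Analysis section of the protocol article fixes one rule for missing data: "an available-case approach for missingness lower than 5% or regression imputations for missingness equal to or higher than 5%, assuming missing at random". It says nothing of a residual term, repeated imputations, the predictors or an ordinal model, and no other section qualifies the rule.

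The same section computes H for the scale, the items and the item pairs, "where H values equal to or greater than 0.3, 0.4, or 0.5 indicate weak, moderate, or strong scales, respectively". Study Design gives the selection of the most scalable items as the reason for choosing Mokken analysis. Reliability follows: "The final set of questions will be used to calculate ρ coefficients for reliability using the Molenaar-Sijtsma technique". No cut-off is set for it. The round 2 CFA is to be estimated by robust maximum likelihood.

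Participants and Procedures states that "automatic data validation checks are included in the survey software to ensure that all responses are complete".

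**The concern.** Every main result of this study is a function of how strongly the items go together. Regression imputation ordinarily means a single predicted value. If the other items are the predictors, each filled-in answer agrees with them without the scatter that a real answer has. The method then adds to the quantity being measured, and more so as more data are missing.

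At stake is which of the 20 items survive into the planned 10 to 15, because an item just under 0.3 can be lifted over it. The published grade and reliability of the scale are also affected, to a lesser degree.

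**Working it through.** **Inputs from the article.** 20 items and n = 500 (Sample Size); five ordered response categories (rating scale in the results); H grades of 0.3, 0.4 and 0.5 and the 5% switch (Data Analysis).

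**Assumptions.** The article gives neither an expected share of missing answers nor an expected H, so there is no figure of its own to reproduce on this point. I assumed 5%, 10% and 20% missing, deleted completely at random, and one-factor data with loadings of 0.4 to 0.7 (H about 0.30) or 0.5 to 0.75 (H about 0.38 to 0.39). The data model described under Sample Size, independent binary items, gives a mean H of about 0 at n = 500, so it cannot serve here. That is a separate matter.

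**Formula.** H = (sum over item pairs of the covariance) / (sum over pairs of the largest covariance that the two items' margins allow).

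**Mechanism.** Let a share f of item X be replaced by its linear prediction from the other items, with squared multiple correlation R².

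- The residual is uncorrelated with the predictors, so the covariance with another observed item Z is unchanged: (1 − f)·cov + f·cov = cov.
- The variance of X falls to [1 − f(1 − R²)]·Var(X).
- The numerator of H holds while the denominator shrinks, so H rises with f. A residual draw with variance (1 − R²)·Var(X) undoes this.

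Now let the only predictor be a covariate whose R² with the trait is 0.10. For imputed cases the covariance with Z is only 0.10 of its true value. At f = 0.10 the numerator is multiplied by 1 − 0.10 × 0.90 = 0.91. The standard deviation of X is multiplied by √[1 − 0.10 × (1 − 0.10λ²)], about 0.95 for loadings λ from 0.4 to 0.7. H therefore falls.

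**Simulation, predictors = the other items (25 runs per row).**

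| Loadings | Missing | H, complete data | H, predicted value | H, prediction rounded to a category | H, with residual draw | Items with H ≥ 0.3: complete → predicted | Rho: complete → rounded |
|---|---|---|---|---|---|---|---|
| 0.4–0.7 | 5% | 0.305 | 0.314 | 0.316 | 0.303 | 10.6 → 12.0 | 0.883 → 0.887 |
| 0.4–0.7 | 10% | 0.300 | 0.319 | 0.322 | 0.297 | 10.1 → 12.2 | 0.880 → 0.889 |
| 0.4–0.7 | 20% | 0.302 | 0.343 | 0.348 | 0.294 | 10.2 → 14.5 | 0.881 → 0.899 |
| 0.5–0.75 | 5% | 0.385 | 0.396 | 0.397 | 0.383 | 19.2 → 19.6 | 0.914 → 0.917 |
| 0.5–0.75 | 10% | 0.393 | 0.414 | 0.418 | 0.389 | 19.6 → 19.8 | 0.916 → 0.922 |
| 0.5–0.75 | 20% | 0.378 | 0.421 | 0.428 | 0.367 | 18.6 → 19.8 | 0.911 → 0.924 |

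- The rise in H is 0.009 to 0.012 at 5%, 0.019 to 0.025 at 10% and 0.041 to 0.050 at 20%. Rounding does not help.
- A separate simulation of the same kind gave 0.294 → 0.306, 0.292 → 0.313 and 0.297 → 0.343. The share of items at or above 0.3 went from about 48% to 55%, 45% to 59% and 48% to 75%.
- With a residual draw the inflation is gone and a slight underestimate remains, at most 0.378 − 0.367 = 0.011.
- Pairwise available-case H stayed within 0.001 of complete data in all six rows.

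**Gaps in five borderline items only** (loadings 0.50 against 0.62 for the other 15; 60 runs). The share of these five reaching 0.3 went from 0.43 to 0.52 at 5%, 0.37 to 0.56 at 10% and 0.41 to 0.76 at 20%. With a residual draw it was 0.42, 0.36 and 0.37.

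**One weak covariate as the only predictor** (R² = 0.10 with the trait; loadings 0.4 to 0.7; 60 runs). H went from 0.306 to 0.292, 0.298 to 0.273 and 0.298 to 0.247 at 5%, 10% and 20%.

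**The case against.** **The article does not say that the residual is left out.** It is a condensed text, and residual, predictors and rounding may be set in a fuller plan. This stands in part: with a residual draw there is no inflation. But the article does fix a method, and the ordinary meaning of its term is a single prediction.

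**The 5% branch may seldom apply to scale items.** The survey software is said to enforce completeness, and the rule also covers self-reported clinical variables such as time in therapeutic range, where gaps are more plausible and H is not involved. This stands and limits the exposure. What remains is mainly survey break-off, which removes blocks of items; the simulation deleted single answers at random and does not model that.

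**Other safeguards exist.** Selection also uses monotonicity and invariant item ordering, and a second sample is used for the CFA. The 0.4 grade is a label with no decision attached. This limits the consequences, but round 2 tests only the items that round 1 kept, and the same imputation rule applies there.

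**Stronger readings that the documents do not support.** A reader might infer:

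- that the bias always flatters the scale. The predictors are unstated, and a weak covariate alone lowers H.
- that inflated reliability gets the scale accepted. Rho is calculated on the final items and has no cut-off, so it is only reported too high. The coefficient for invariant item ordering does have a cut-off, but it was not simulated and nothing is claimed for it.
- that the branch below 5% discards most of the sample. With 4% independent gaps on each of 20 items, complete-case analysis would leave 0.96^20 = 0.442, or 221 of 500. The article says available-case, and pairwise H needs no such loss.
- that the rule contradicts itself on the missingness mechanism. The missing-at-random assumption can be read as belonging to the imputation branch alone.

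**Conclusion.** The point holds in a limited form. On its usual reading, with the other items as predictors, the stated rule biases H upward by about 0.01 at 5% missing, 0.02 at 10% and 0.04 to 0.05 at 20%. At 5% to 10% that is modest, yet it moved one to two more of 20 items to 0.3 or above when H was near 0.30 (10.6 to 12.0; 10.1 to 12.2). It also moved a scale at 0.393 to 0.414. Rho rose by 0.003 to 0.018.

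The switch also works the wrong way round under these conditions: it leaves an approach that showed almost no bias for one that did, just as missingness grows.

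The sizes rest on assumed loadings and missingness rates, deletion completely at random and few runs per setting. The direction depends on the predictors, and the practical effect on how much item data is in fact missing. It should be changed, but it does not threaten the study as a whole.

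**What to change.** Drop single regression imputation of scale items, and drop the 5% switch.

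- **Round 2 CFA:** fit the robust maximum likelihood model already planned to all observed responses (full information, assuming missing at random), with no prior imputation.
- **Round 1 Mokken analysis:** use multiple imputation of ordinal item scores, or at least stochastic imputation with a residual draw. Name the other items as predictors and, with multiple imputation, pool H and rho over the imputations. Pairwise available-case H is an acceptable alternative.
- **Sensitivity:** report complete-case H beside the main result.

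If a residual draw was intended all along, the text should say so and name the predictors.

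The cost is a change of wording and modest programming; no further data are needed. H and reliability may come out slightly lower than under the present rule.

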### Ethical Considerations

The present protocol was approved by the Ethical Committee of Ospedale San Raffaele (protocol number 52/INT/2023). Ethical considerations will be carefully adhered to throughout the research process.

In the first stage of the study, which involves experts assessing the content validity [29,30], written informed consent will be obtained from each expert. They will be fully informed about the study’s objectives and their voluntary participation in the process. During the second part of the study, data collection will be carried out through anonymous web surveys. As per European Regulation 2016/679 and Legislative Decree 101/2018, this type of study ensures anonymity and does not require individual written informed consent from the participants [31]. However, to ensure transparency and participant understanding, a simple and clear presentation page will be provided to patients before they proceed to complete the web-based questionnaire. This page will explain the study’s purpose, the voluntary nature of their participation, and the anonymity of the survey.

The research team will prioritize the confidentiality and privacy of all participants involved in the study, adhering to the ethical principles outlined in the Declaration of Helsinki. Personal data will be handled with utmost care, and all data collected will be stored securely and accessible only to authorized personnel involved in the study. Any potentially identifying information will be removed from the dataset to ensure complete anonymity. Throughout the study, participants’ rights and welfare will be protected, and any potential risks will be minimized. The study findings will be reported and disseminated in a manner that preserves anonymity and confidentiality. Researchers will act responsibly, maintaining the highest ethical standards and ensuring that the study is conducted with integrity and respect for the participants’ rights and well-being.

**Conceptual framework**
Defined by the literature summarized in a literature review published elsewhere, describing self-care behaviors in patients on oral anticoagulant therapy [13].
**Focus of PERSONAE measure**
Assess how ready patients feel about undertaking and managing the tasks associated with their anticoagulation therapy by translating the behavioral content identified in the review into terms of preparedness (refer to Multimedia Appendix 1).
**Item pool drafting**
November 2023
**Expert panel for validation**
Date of content validation: December 2023.Median age: 36 (IQR 29-45) years.Education qualifications: 25% (n=3) with a master of science, 25% (n=3) with a doctor of philosophy, and 50% (n=6) medical doctors.Specialties: 16.67% (n=2) in cardiology, 50% (n=6) in nursing, 16.67% (n=2) in pharmacy, and 16.67% (n=2) in internal medicine.Experience: All experts with more than 6 years in oral anticoagulation.Sex distribution: 66.67% (n=8) females.Conflict of interest: None reported (100%, n=12).Content: 50% (n=6) in nursing, 16.67% (n=2) in pharmacy, and 16.67% (n=2) in internal medicine.Experience: all experts with more than 6 years in oral anticoagulation.Sex distribution: 66.67% (n=8) females.Conflict of interest: none reported (100%, n=12).Content validity ratio (CVR): All 20 items obtained adequate CVR (refer toMultimedia Appendix 1for additional details).
**Scale question**
“How prepared do you feel to independently monitor and manage your oral anticoagulation therapy for each of the following statements?”
**Rating scale**
A 5-point Likert scale ranging from 1 (not at all prepared) to 5 (extremely prepared).
**Data collection for phase 2**
Ongoing, anticipated completion by September 2024.
**Impact of PERSONAE scale**
The PERSONAE scale will offer a comprehensive and validated tool to assess the preparedness of patients for self-monitoring and self-management of oral anticoagulation, aiding clinicians in tailoring interventions. Health care providers can empower patients to take an active role in their anticoagulation therapy, potentially improving treatment outcomes and reducing health care costs by encouraging safe and effective practices of self-monitoring and self-management.
**Dissemination of results**
Upon successful validation, the results will be disseminated through peer-reviewed publications and presentations at international conferences. The research team plans to engage with professional societies and patient advocacy groups to promote the implementation of the PERSONAE scale in clinical practice globally.

The conceptual framework was defined by the literature summarized in a literature review published elsewhere, describing self-care behaviors in patients on oral anticoagulant therapy [13]. The focus on preparedness encapsulates the ability to perform specific self-care tasks and integrates the confidence and knowledge necessary to manage treatment proactively. In other terms, the version of the PERSONAE measure derived from phase 1 aims to assess how ready patients feel about undertaking and managing the tasks associated with their anticoagulation therapy by translating the behavioral content identified in the review into terms of preparedness (Multimedia Appendix 1). Once the pool of items was drafted (November 2023), an expert panel for validating the PERSONAE scale was involved, and it consisted of 12 professionals with diverse qualifications and backgrounds in health care. The process of content validation was performed in December 2023. The median age of the experts was 36 (IQR 29-45) years. Regarding higher education qualifications, 25% (3/12) held a master of science degree, another 25% (3/12) had earned a doctor of philosophy degree, and the remaining 50% (6/12) were medical doctors. Expertise among the panel members varied, with representation from multiple disciplines critical to managing oral anticoagulation therapy. Specifically, 16.67% (2/12) specialized in cardiology, the majority, 50.00% (6/12), were from nursing, 16.67% (2/12) practiced pharmacy, and 16.67% (2/12) were from internal medicine. When considering potential conflicts of interest, it was noted that 100% (12/12) of the experts reported none. All experts had substantial experience with oral anticoagulation, with each member having more than 6 years of experience in the field, which provided a solid foundation for their evaluative contributions. Regarding sex distribution, the panel was predominantly female, with 66.67% (8/12) of the members being women. All content validity ratio (CVR) of the 20 items obtained adequate content validity based on the evaluation of the experts (Multimedia Appendix 1; all observed CVR were equal or higher to the critical CVR, indicating the minimum level of agreement among the experts for an item to be considered essential beyond the level of chance at a significance level of .05 for a 1-tailed test).

The question guiding the self-report assessments derived from phase 1 is: “How prepared do you feel to independently monitor and manage your oral anticoagulation therapy for each of the following statements?” Therefore, the scale is designed for the patients. In the current form of the scale, patients are asked to rate their level of preparedness on a 5-point Likert scale ranging from 1 (not at all prepared) to 5 (extremely prepared). Therefore, the scale prompts patients to consider their proficiency across a spectrum of 20 activities (items) vital to the effective self-management of their treatment, from medication adherence to lifestyle adjustments and the use of technology.

The data collection for phase 2 is ongoing, and it is anticipated to be completed in September 2024. The PERSONAE scale will fill a critical gap by offering a comprehensive and validated tool to assess the preparedness of patients for self-monitoring and self-management of oral anticoagulation. Clinicians will be able to use this scale to identify patients who may benefit from self-testing approaches and tailor interventions accordingly. Health care providers can empower patients to take an active role in their anticoagulation therapy, potentially improving treatment outcomes and reducing health care costs by encouraging safe and effective practices of self-monitoring and self-management.

Upon successful validation, the results will be disseminated through peer-reviewed publications and presentations at international conferences. The research team plans to engage with professional societies and patient advocacy groups to promote the implementation of the PERSONAE scale in clinical practice globally.

